### Schedule of Assessments

Assessments are conducted at baseline (before randomization and before surgery) and at weeks 2 and 26 after enrollment (Table 3).

**Table 3. pnac138-T3:** Schedule of assessments for the MIND-PT trial

Outcome	Screening	Baseline Assessment	Postsurgery Assessment at 2 Weeks After Surgery	Postsurgery Assessment at 26 Weeks After Surgery
		(days ^−^30–0)	(days 10–30)	(days 160–200)
Informed consent	X			
Eligibility criteria	X			
Demographics		X		
Medical history		X		
PEG (primary outcome)*		X	X	X
TAPS Substance Use Screener*		X		
PROMIS—Pain Interference short form		X	X	X
PROMIS—Physical Function short form*		X	X	X
PROMIS—Sleep Disturbance short form*		X	X	X
PHQ-2 depression screener*		X	X	X
GAD-2 anxiety screener*		X	X	X
High-impact chronic pain		X		X
Pain self-efficacy		X	X	X
Pain catastrophizing*		X	X	X
Patient global impression of change*				X
Health care utilization for back pain^†^				X
Opioid discontinuation^†^				X

* Indicates an NIH HEAL initiative core domain for assessment of adult chronic pain [56].

† Indicates some aspects of the data element are collected from the electronic health record.

### Outcomes

Outcome measures for the MIND-PT study are compliant with the common data elements established by the National Institutes of Health Helping to End Addiction Long-term (NIH HEAL) initiative. The NIH HEAL initiative identified nine core domains for pain assessment [56] with corresponding questionnaires [57] that are included in this study (Table 3).

#### Primary Outcome

The primary outcome is the Pain, Enjoyment, and General Activity (PEG) Scale at 26 weeks. The PEG includes three items evaluating 1) pain severity on average in the prior week, 2) interference of pain with enjoyment, and 3) interference of pain with general activity. Response options for each item range from 0 to 10, and the PEG score is expressed as the mean of all item scores [58]. The minimally important difference for the PEG is estimated as 1.0 [59]. Variability, assessed as standard deviations, ranges from 2.0 to 2.2 for baseline scores and from 2.5 to 2.8 for change scores in groups receiving an effective intervention [58, 60].

#### Main Secondary Outcome

Time to opioid discontinuation will be the main secondary outcome. Opioid use will be determined from the Pharmacy Data Transaction Service data table of the Military Health System Data Repository. The Military Health System Data Repository contains TRICARE claims for inpatient and outpatient encounters provided in military or civilian facilities. The unique number of prescriptions and total days’ supply will be extracted for all prescriptions involving opioid partial agonists or agonists in categories II, III, or IV. Time to discontinuation will be defined as the days’ duration between the date of surgery and a period of 31 days after surgery with no opioid fill and no additional fills beyond the 31st day. When this definition is met, the 31st day from the last fill is the date of discontinuation [5].

#### Additional Secondary Outcomes

Additional NIH HEAL core outcome domains include Patient-Reported Outcomes Measurement Information System (PROMIS) short forms assessing pain interference (4a), physical function (6b), and sleep disturbance (6a). All PROMIS scores are reported on a T-score metric, with a score of 50 points aligning with the general population mean and a standard deviation of 10 [61]. The General Anxiety Disorder two-item screener (GAD-2) and the Patient Health Questionnaire two-item mood screener (PHQ-2) are used to identify general anxiety and depression, respectively. The GAD-2 and PHQ-2 each have two items with response options ranging from 0 to 3. A score of 3 or more has been used to identify possible cases of generalized anxiety disorder on the GAD-2 [62]. For the PHQ-2, a score of 3 or more is associated with a major depressive episode [63]. The Tobacco, Alcohol, and Prescription Medications and other Substance (TAPS) Tool is a four-item screening for tobacco use, alcohol use, prescription medication misuse, and illicit substance use in the prior year. Each item has five response options ranging from “daily or almost daily” to “never.” Responses other than “never” are considered a positive screen [64]. The Pain Catastrophizing Scale (PCS-6) and Self-Efficacy (PSEQ-4) short-form questionnaires are used to evaluate a participant’s negative cognitive–affective response to anticipated or actual pain and their confidence in performing activities despite pain, respectively [65]. High-impact chronic pain is identified from two questions: 1) “In the past 3 months, how often did you have pain?” and 2) “Over the past 3 months, how often did pain limit your life or work activities?” Responses of “most days” or “every day” to both questions identifies high-impact chronic pain [66]. The single-item Patient Global Impression of Change measure assesses participants’ global impression of change after treatment on the basis of the question, “Since the time period right before I had surgery, my overall pain is …,” with Likert scale response options ranging from (1) “very much worse” to (7) “very much improved.”

### Statistical Methods

Analyses for the project aims are outlined below. Intention-to-treat principles will guide the analyses, with patients evaluated on the basis of randomized assignment regardless of compliance.

#### Aim 1 (Primary)

The primary aim compares the effectiveness of two pain management pathways (UC vs EPM). The primary effectiveness end point will be change in PEG score at 26 weeks after surgery. The primary analysis will be performed by fitting a longitudinal linear model to the PEG scores at baseline and at the 2- and 26-week follow-ups [67]. Application of a longitudinal analysis, rather than performance of separate analyses for each time point, will better account for missing data [68]. The longitudinal model assumes equal mean baseline PEG scores across treatment arms [69]. An unstructured covariance matrix will be used to account for correlation of serial measures in the same subject to avoid imposing specific assumptions about distributions of random effects [70]. The longitudinal model will include fixed effects for randomized treatment group, visit time (as a category variable), and the group×time interaction. The model will also include covariates for the randomization stratification factors and their interactions with visit time. The primary assessment of effectiveness will be based on a linear contrast comparing adjusted mean PEG scores at 26 weeks between groups. Additional linear contrasts will assess effectiveness on the 2-week PEG score and will evaluate whether the magnitude of the effect of EPM compared with UC changes between the 2- and 26-week assessments.

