**Figure 1. pnac138-F1:**
[figure not shown]
Biopsychosocial paradigm relating cognitive and emotional responses to pain to outcomes.

The relevance of the biopsychosocial model to patients receiving spine surgery is supported by evidence that pain catastrophizing, low self-efficacy, and hypervigilance predict poor postsurgical outcomes [32–34]. These factors also predict long-term postsurgical opioid use [35, 36]. Spine surgery can exacerbate catastrophic thinking [37, 38], especially if patients have unrealistic recovery expectations that go unmet [39, 40]. Nonpharmacological treatments have the potential to disrupt the cycle of catastrophic appraisals, low self-efficacy, and hypervigilance that can reinforce overreliance on opioid medication. Positive effects of physical therapy (PT) for LBP are mediated through changes in pain catastrophizing and self-efficacy [41–44]. Mindfulness, which involves the generation of temporary states of monitoring mental experiences and sensory information without evaluation, reduces pain attentional bias and disentangles the pain experience from associated emotions and catastrophic appraisals [45]. The effects of mindfulness on reducing chronic pain severity are mediated by shifting from emotional to sensory processing of the pain experience [46, 47], and mindfulness-based interventions can increase self-awareness and self-regulation of conditioned, automatic habits like opioid use [48, 49] and reduce reactivity to opioid-related cues (e.g., the sight of an opioid pill bottle) [50]. Given these complementary mechanisms, integrating PT and mindfulness techniques might be particularly beneficial for persons with chronic pain undergoing surgery, but this premise has not been evaluated.

The purpose of the present article is to describe the MIND-PT study, which will evaluate a nonpharmacological strategy that integrates PT and mindfulness in an enriched pain management pathway for patients undergoing lumbar surgery. The enriched pathway threads consistent messages and techniques focused on developing non-opioid pain coping strategies from the presurgery to postsurgery periods to improve surgical outcomes and reduce risk of persistent opioid use. We will compare the enriched pathway to usual-care pain management.

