### Screening, Recruitment, and Randomization

Recruitment will occur among patients scheduled for lumbar surgery, including fusion, laminectomy, decompression, or discectomy, at recruitment sites. Potential participants will be identified as they schedule for surgery. When a patient is scheduled for surgery, they are entered into a pathway that involves follow-up assessments and a final presurgical visit. The study team will maintain communication with the surgical team to receive referrals of patients to the study. In addition to efforts for direct referral, we will secondarily identify potential participants from the surgical roster for future surgeries from the surgical scheduling system. A Health Insurance Portability and Accountability Act (HIPAA) waiver allows approved research staff to review the appointment list in the Military Health System electronic health record. Scheduled patients may be notified of the study and their potential eligibility. Interested individuals will meet with a site research assistant who will facilitate the informed consent process.

Treatment assignment will occur after consent and baseline assessment are complete. Individual participant randomization with 1:1 distribution will be administered with the REDCap randomization module (Vanderbilt University, Nashville, TN, USA). A study statistician created a randomization allocation table by using blocked randomization with block sizes of 4 or 6. Randomization is stratified by recruitment site, presurgery opioid use (yes/no), and type of surgery (planned with or without fusion). The allocation table was prepared with SAS software version 9.4 (SAS Institute Inc., Cary, NC, USA).

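### The primary PEG model is valid but leaves out two baseline scores that the protocol itself treats as prognostic: a possible, unquantified gain in precision, not an error

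*Protocol article*

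**What the plan says.** Aim 1 (Primary) sets out the model term by term. "The longitudinal model will include fixed effects for randomized treatment group, visit time (as a category variable), and the group×time interaction". Then: "The model will also include covariates for the randomization stratification factors and their interactions with visit time". Under Screening, Recruitment, and Randomization the stratification factors are recruitment site, presurgery opioid use and planned fusion. Baseline PEG is handled through a constraint: "The longitudinal model assumes equal mean baseline PEG scores across treatment arms". With an unstructured covariance, this adjusts the 26-week contrast for baseline PEG. No other baseline covariate is listed for this model.

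Elsewhere, Background and Rationale (the text after Figure 1) cites evidence that "pain catastrophizing, low self-efficacy, and hypervigilance predict poor postsurgical outcomes". Additional Secondary Outcomes names the instruments: "The Pain Catastrophizing Scale (PCS-6) and Self-Efficacy (PSEQ-4) short-form questionnaires". Table 3 (Schedule of Assessments) has the rows "Pain catastrophizing" and "Pain self-efficacy", both marked at baseline, 2 weeks and 26 weeks. The text above that table places the baseline assessment before randomization and surgery, and treatment is assigned only once that assessment is complete.

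**The concern.** In a randomized trial analysed with a linear model, a prespecified baseline covariate that predicts the outcome does not bias the treatment contrast, and it reduces residual variance. The protocol asserts that two of its own baseline measures are prognostic, schedules them for everyone before assignment, and then does not use them in the primary contrast. If they predict 26-week PEG beyond what baseline PEG and the strata already explain, the confidence interval is a little wider than the collected data require. A chance imbalance between arms in these scores would also be only partly adjusted for, through their correlation with baseline PEG and the strata. The choice has to be made before outcomes are seen, because the same adjustment made later would be post hoc.

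**Working it through.** **Inputs from Sample Size Determination:** difference 1.0, SD 2.5, alpha 0.05 (taken as two-sided; the section does not say), 80% retention, serial correlation 0, and 136 per group for 80% power.

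**Inputs assumed, because the document gives neither:** rho, the correlation of baseline with 26-week PEG, at 0, 0.3 and 0.5; and R², the partial R-squared of baseline PCS-6 plus PSEQ-4 given baseline PEG and strata, from 0 to 0.10.

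**Step 1. The plan's own figure.** n per arm = 2(1.960 + 0.842)² × 2.5² / 1.0² = 98.1, rounded up to 99. Dividing by 0.80 gives 124 per arm (125 with the t distribution), against the stated 136. The stated figure is not reproduced, but it errs on the safe side. With 136 × 0.80 = 108.8 analysed per arm, SE = 2.5 × √(2/108.8) = 0.339 and power = Φ(1.0/0.339 − 1.960) = 83.9%. The point here does not depend on this discrepancy.

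**Step 2. Effect of the two scores.** Residual SD = 2.5 × √[(1 − rho²)(1 − R²)]. Power is then as in step 1, and the 95% CI half-width is 1.96 × SD × √(2/108.8).

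| rho | Power at R² = 0 | R² = 0.02 | R² = 0.05 | R² = 0.10 | CI half-width, R² = 0 to 0.10 |
|---|---|---|---|---|---|
| 0 | 83.9% | 84.6% | 85.7% | 87.5% | 0.664 to 0.630 |
| 0.3 | 87.1% | 87.8% | 88.7% | 90.3% | 0.634 to 0.601 |
| 0.5 | 92.6% | 93.1% | 93.8% | 94.9% | 0.575 to 0.546 |

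**Step 3. The same gain in participants.** The equivalent increase in sample size is 1/(1 − R²) − 1, whatever rho is: 0% at R² = 0, 2.0% at 0.02, 5.3% at 0.05 and 11.1% at 0.10. On 272 participants, 5.3% is about 14 and 11.1% is about 30.

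**Step 4. How large R² might be.** For one score X, 26-week PEG Y and baseline PEG P, the partial correlation is (r_YX − r_YP × r_XP) / √[(1 − r_YP²)(1 − r_XP²)]. Illustrative correlations give:

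- r_YP = 0.4, r_YX = 0.2, r_XP = 0.5: partial R² = 0.000
- r_YP = 0.4, r_YX = 0.3, r_XP = 0.5: partial R² = 0.016
- r_YP = 0.3, r_YX = 0.4, r_XP = 0.3: partial R² = 0.116

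A plausible raw correlation with outcome can therefore shrink to nothing once baseline PEG is in the model. It can also slightly exceed 0.10 in a favourable case. The range of 0 to 0.10 is a working assumption, not a bound taken from the document.

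**Step 5. Cost in parameters.** Two scores across three visits add six mean parameters, against about 218 analysed participants (2 × 108.8).

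**The case against.** The strongest reply is that nothing here is wrong. The model already adjusts for the outcome's own baseline and for every stratification factor, each by visit. Calling a trait predictive in a background section does not oblige the plan to adjust for it. This stands.

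The background sentence also concerns poor postsurgical outcomes in general. It gives no correlation with PEG and does not say that prediction persists after adjustment for baseline pain. Two of the three PEG items measure pain interference, so overlap with catastrophizing and self-efficacy is plausible and the gain could be near zero. This stands too.

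The row at rho = 0 shows the gain in power near its most favourable. The sample size section itself expects positive correlation, and it is strained to suppose that baseline PEG explains nothing while two related scores explain 10%. The rows at 0.3 and 0.5 are the more realistic ones.

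The imputation section allows unnamed auxiliary variables. If these include the two scores, they may recover some precision for the roughly 20% assumed missing, but they do not reduce residual variance among participants whose PEG is observed.

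Two replies do not hold. The mediators in Aim 2 are changes from baseline to week 2, whereas baseline values precede assignment and cannot be affected by it. A fuller analysis plan, not shown, might add covariates, and that would settle the point; but the article's list reads as complete.

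A reader might infer that the primary analysis is biased or underpowered, or that the background contradicts the model. The document supports none of these. The contrast is valid, power is about 84% even at zero correlation, and the standard error already allows for random imbalance.

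**Conclusion.** The point holds as an optional improvement of low priority. The planned primary analysis is sound. Adding the two baseline scores would be worth between nothing and about 11% more participants if their partial R-squared lies between 0 and 0.10. In power that is at most about 3.6 points at zero serial correlation (83.9% to 87.5%), 3.2 at 0.3 (87.1% to 90.3%) and 2.3 at 0.5 (92.6% to 94.9%). The 95% CI half-width would shrink by about 0.03 PEG points at best, against a minimally important difference of 1.0. These figures rest on assumed values of rho and R², a two-sided test, 80% retention and a normal approximation that ignores any information from the 2-week visit. The direction of the gain is secure if the scores are prognostic given baseline PEG. Its size is unknown.

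**What to change.** Before unblinding, add to the Aim 1 (Primary) model the baseline PCS-6 and baseline PSEQ-4 scores, each with its interaction with visit. Keep the model as now written as a sensitivity analysis. Four details belong with the change:

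- Use baseline values only. The week-2 scores are measured after randomization and must not enter the primary model.
- Aim 1 (Other Secondary Analyses) reuses similar models for the other patient-reported outcomes, including these two. State that a score is not a covariate in the model where it is the outcome.
- Handle any missing baseline scores through the multiple imputation already planned.
- Aim 1a repeats the Aim 1 model and Aim 2 draws on it, so state whether the added covariates carry over to each.

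The cost is a short addition to the analysis text and a few degrees of freedom, with no new data, visits or participants. The downside is that the gain may prove negligible.

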#### Aim 1 (Main Secondary)

Time to opioid discontinuation is the main secondary outcome and is defined as the time between the date of surgery and a period of 31 days after surgery with no opioid fill and no additional fills beyond the 31st day. When this definition is met, the 31st day from the last fill is the discontinuation date [5]. Kaplan-Meier curves with 95% pointwise confidence limits will be constructed to summarize the time to opioid discontinuation in each treatment group. Between-group comparison will use a stratified log-rank test, stratified by the three randomization stratification factors. We will also carry out a companion stratified Cox proportional-hazards regression analysis to express the treatment effect on time to opioid discontinuation as a hazard ratio. The log-rank test and Cox regression analyses will be right-censored at the date of last opioid use assessment for patients with premature loss-to-follow-up and at 26 weeks for patients who complete their 26-week follow-up period without opioid discontinuation.

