## Background and Rationale

Chronic pain is a common and consequential condition for civilian and military populations. Low back pain (LBP) is the most common chronic pain diagnosis and the most common diagnosis associated with an opioid prescription in both military and civilian health care [1–3]. Because of its high prevalence and its contribution to concerns about opioid overprescribing, improving the management of chronic LBP is a priority across health care settings [4–6].

A small percentage of persons with chronic LBP receive surgery, but many have used opioids long term for pain management [7–9]. Recent studies indicate that a third to half of persons undergoing elective spine surgery have used opioids long term, and most will receive at least one postoperative prescription [8, 10]. Despite optimism from providers and patients that surgery will eliminate the need for long-term opioid use, most persons who used opioids long term before surgery persist in use, even 2 years after surgery, some at increased dose [10–12]. Presurgical opioid use is also associated with worse functional outcomes, increased rates of complications, and higher medical costs [11, 13–15]. Persistent postsurgical opioid use is associated with increased risk of interventional pain procedures, re-operation, opioid-related adverse events, and higher medical costs [11, 16]. These findings indicate that outcomes after lumbar surgery will not improve without a comprehensive strategy for better pain management that prepares patients to manage pain without overreliance on opioids.

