### Study Population

The MIND-PT study is designed to recruit a representative cohort of active-duty military, family members of active-duty personnel, and retirees who are TRICARE beneficiaries scheduled for lumbar surgery in a military or civilian hospital. Specific eligibility criteria are outlined in Table 1. Participants will also be identified as meeting criteria for long-term opioid use before surgery, as these patients could be at the highest risk of postsurgical long-term opioid use [10, 12].

**Table 1. pnac138-T1:** Eligibility criteria for the MIND-PT trial

Inclusion Criteria	Exclusion Criteria
1. Active-duty military or member of Reserves or National Guard on active duty, family member of active-duty personnel, or other TRICARE beneficiary receiving care in a participating facility.	1. Indication for surgery is infection, fracture, tumor, trauma, or other indication requiring emergency surgery.
2. Age 18–75 years.	2. Surgical procedure is a revision, or individual has undergone a lumbar surgical procedure in the past year.
3. Scheduled to undergo lumbar spine surgery within the next 60 days. Surgery may be a microdiscectomy, discectomy, or laminectomy with or without fusion, including lateral, transforaminal, posterior, or anterior approach for 1–4 lumbar levels. Procedure may be performed in a military or civilian hospital.	3. Contraindication to participation in postoperative exercise program, including severe orthopedic injury limiting mobility, wheelchair dependency, neurological disorder impacting mobility, reliance on supplemental oxygen for daily activity, etc.
4. Anticipates ability to attend treatment sessions over a 16-week period after the surgical procedure, with no planned absence of 2 weeks or more for training, vacation, or any purpose.	4. Pending a medical evaluation board, discharge from the military for medical reasons, or pending or undergoing any litigation for an injury.
5. Able to speak and read English well enough to provide informed consent, follow study instructions, and independently answer surveys	

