#### Aim 1a (Subgroup Analysis)

Subgroup analysis will be performed by repeating the Aim 1 longitudinal analysis within prespecified subgroups based on presurgical opioid risk (high/low) and extending the model by adding a main effect term for opioid risk, as well as the interaction between treatment group and opioid risk. Results of the subgroup analysis will be assessed primarily on the basis of the treatment×subgroup interaction, using a two-sided α = 0.05. We will also add similar main effect and interaction terms to the Cox regression analysis of time to discontinuation of opioid use and to the logistic regression analysis of opioid use at 26 weeks to evaluate treatment effect heterogeneity on the opioid use outcomes.

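### The main opioid comparison controls presurgical exposure only through the yes/no randomisation factor and leaves unused a long-term-use variable that the trial already records; the test is valid but may lose power

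*Protocol article*

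**What the plan says.** All references are to the protocol article.

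- **Aim 1 (Main Secondary)** fixes the test: "Between-group comparison will use a stratified log-rank test, stratified by the three randomization stratification factors". It adds: "We will also carry out a companion stratified Cox proportional-hazards regression analysis to express the treatment effect on time to opioid discontinuation as a hazard"; the measure meant is the hazard ratio. No further covariate is named for either analysis.
- **Screening, Recruitment, and Randomization** gives the factors: "Randomization is stratified by recruitment site, presurgery opioid use (yes/no), and type of surgery (planned with or without fusion"). Opioid use is not defined further.
- **Study Population** describes a baseline classification: "Participants will also be identified as meeting criteria for long-term opioid use before surgery, as these patients could be at the highest risk"; the risk meant is that of long-term use after surgery.
- **Background and Rationale** says that "a third to half of persons undergoing elective spine surgery have used opioids long term", and that "most persons who used opioids long term before surgery persist in use, even 2 years after surgery, some at increased dose".
- **Aim 1a (Subgroup Analysis)** brings opioid risk (high/low) into the time-to-event model: "We will also add similar main effect and interaction terms to the Cox regression analysis of time to discontinuation of opioid use". Its stated purpose there is to assess heterogeneity of the treatment effect.

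**The concern.** By the article's own account, long-term use before surgery predicts the event being analysed, and it is known at baseline. The overall comparison uses only the yes/no factor. If *yes* covers any use, someone with one short course and someone on opioids long term sit in the same stratum.

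Mixing unequal discontinuation hazards within a stratum pulls the estimated hazard ratio toward 1 and lowers power. The primary analysis, by contrast, models each patient's baseline PEG score. At stake is the efficiency of the trial's main opioid result, for which the article gives no power figure.

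**Working it through.** **The article's own figure.** The only power calculation concerns PEG. With a difference of 1.0, SD 2.5, two-sided alpha 0.05 and 80% power:

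- n = 2 × (1.960 + 0.842)² × 2.5² / 1.0² ≈ 98.1, so 99 evaluable per group.
- 99 / 0.80 = 123.75, so 124 per group, against 136 stated.
- 136 × 0.80 = 108.8 evaluable per group gives about 84% power.

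The stated size is thus somewhat larger than its inputs require. This does not bear on the opioid outcome, which has no stated figure to reproduce.

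**Inputs from the article.** N = 272; 1:1 allocation in blocks of 4 or 6 within site, opioid yes/no and fusion; censoring at 26 weeks; 80% retention, carried over here as 20% dropout.

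**Assumptions not in the article.** Hazard ratio 1.5; three sites with no site effect; half of patients with fusion, and a hazard 1.4 times higher without fusion; exponential event times; *yes* means any use. User shares and 26-week discontinuation under usual care are varied in the table. The long-term shares of 35% and 50% reflect the background range of a third to a half. Long-term discontinuation of 25 to 45% reflects the statement that most persist.

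**Step 1: hazard contrast inside the *yes* stratum.** With hazard = −ln(1 − proportion discontinuing), the ratio of other users to long-term users is:

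- 85% v 25%: 1.897 / 0.288 = 6.6
- 85% v 40%: 1.897 / 0.511 = 3.7
- 70% v 40%: 1.204 / 0.511 = 2.4
- 60% v 45%: 0.916 / 0.598 = 1.5

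**Step 2: benchmark.** Eighty per cent power at hazard ratio 1.5 needs 4 × (1.960 + 0.842)² / (ln 1.5)² ≈ 191 events. The first setting below yields about 196. With equal risk within strata, power would be about Φ(0.4055 × √196 / 2 − 1.960) = Φ(0.88) ≈ 81%.

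**Step 3: simulated power.** The planned stratified log-rank test is compared with a score test that keeps the planned strata and adds long-term use as a Cox covariate. There were 3,000 trials per row; gains are from unrounded figures.

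| Shares: none / other / long-term (%) | Discontinuing, same order (%) | Planned (%) | With covariate (%) | Gain (points) |
|---|---|---|---|---|
| 35 / 30 / 35 | 95 / 85 / 40 | 69.5 | 77.2 | 7.7 |
| 35 / 30 / 35 | 95 / 85 / 25 | 60.4 | 73.4 | 13.0 |
| 35 / 30 / 35 | 90 / 70 / 40 | 73.0 | 75.2 | 2.2 |
| 35 / 30 / 35 | 90 / 60 / 45 | 74.3 | 74.4 | 0.2 |
| 30 / 20 / 50 | 95 / 85 / 40 | 65.5 | 72.7 | 7.2 |
| 50 / 15 / 35 | 95 / 85 / 40 | 72.8 | 76.2 | 3.5 |
| 50 / 15 / 35 | 90 / 60 / 45 | 77.1 | 77.0 | −0.1 |

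The last row is no difference within simulation error. Variants of the first row:

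- Six sites: 65.8% to 73.0%.
- Hazard ratio 1.3: 34.7% to 41.2%.
- No treatment effect (6,000 trials): rejection 4.9% planned, 5.0% with the covariate.
- *Yes* meaning long-term use only (65% *no*, 35% *yes*): 81.0% both ways.

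**Step 4: a third stratum level instead of a covariate.** In the first setting, splitting *yes* into two strata raises log-rank power from 69.4% to 75.3%, less than the covariate's 77.2%. At 90 / 60 / 45% discontinuation it loses power as sites increase: 70.4% to 67.8% with six sites, and 64.8% to 60.3% with ten (67.1% to 62.9% in a second run). The article does not state the number of sites.

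**The case against.** The strongest objection concerns the definition. The article never says that *yes* means any use. The factor could be the long-term classification itself, in which case a long-term indicator gains nothing. The Study Population section says long-term users will *also* be identified, and the randomisation section uses a different term. Both favour two separate classifications, but that is inference. An article may also leave the definition to the full protocol, so its absence is not a fault. This objection stands, and it makes the point conditional.

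Second, stratifying by the randomisation factors is standard, and covariates for secondary outcomes are often left to the analysis plan. That is fair as far as it goes. Here, though, the article does fix the main test and its strata, so the choice can be judged.

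Third, Aim 1a already puts opioid risk in the Cox model. It does so to examine the interaction, which does not sharpen the overall comparison.

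Fourth, the gain rests on assumed rates and nearly vanishes when other users often continue too. The background shares describe elective spine surgery generally, whereas this trial excludes revisions and recent lumbar surgery. This stands as a limit on size.

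A reader might also infer that the planned test is biased, because long-term users may be unevenly split within the *yes* stratum. The simulation does not support that: such imbalance is ordinary randomisation variability, and type I error is nominal.

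**Conclusion.** The point holds as one of avoidable inefficiency. If *yes* means any use, the planned test is valid but forgoes about 0 to 13 points of power at hazard ratio 1.5. The gain is about 3 to 13 points where other users mostly stop (85%) and most long-term users persist, and about 0 to 3 points where the two groups differ less. If *yes* already means long-term use, a long-term indicator adds nothing. The hazard ratio, user shares, discontinuation rates and site count are all assumptions.

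Two stronger readings should be resisted. The article supports calling long-term use strongly prognostic and already recorded; it does not show that it is the strongest predictor. Nor is every finer adjustment free: the covariate showed no loss beyond simulation error, but a third stratum level can reduce power.

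**What to change.** In Aim 1 (Main Secondary), keep the three randomisation strata and prespecify long-term presurgical opioid use, fixed as of randomisation, as a covariate in the stratified Cox model. Name that model's treatment test as the main opioid comparison, and keep the planned stratified log-rank test as a sensitivity analysis. Do not add a third opioid stratum level.

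State what the yes/no factor means. If it already means long-term use, use the log of presurgical days' supply from the pharmacy data as the covariate instead. The gain from that version was not computed.

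The cost is about a sentence in the plan, settled before any outcome data are examined by arm. Long-term use is already to be identified; the days' supply version draws on the pharmacy source already in use and needs a stated look-back window. The downside is small: the hazard ratio becomes conditional on long-term use, and the model assumes proportional hazards for that covariate.
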